### 2.5. Eligibility Criteria

Participants are eligible if they are at least 18 to 70 years old, have been diagnosed with sleep-onset insomnia or a self-reported insomnia diagnosis (Insomnia Severity Index score ≥ 15), have sleep onset latency > 30 min 6 months prior to enrollment, and no pharmacologic or non-pharmacologic treatment for insomnia in the last 14 days, including sedating medications at bedtime. Patients who meet any of the exclusion criteria (see Table 1) on the day of consent will be excluded.

After potential participants are selected, the study team will obtain informed consent approved by the USU Institutional Review Board (IRB). Participants will be free to withdraw consent and discontinue participation at any time without prejudice. In addition, the PI may end a participant’s participation in this study for any of the following reasons: (1) if the participant develops any condition that in the judgment of the PI may place them at risks not described above or at greater severity for those described above by continuing his/her participation; (2) if the participant becomes pregnant; (3) if the participant is unable to keep his/her scheduled sessions; (4) if the study is halted by the sponsor, the IRB, or the FDA; and (5) for administrative reasons.

### 2.6. Sample Size

Our trial design was motivated by a power analysis based on the results of a smaller investigational study conducted by Teledyne. A sample size estimation was carried out comparing the mean SOL between the sham and stimulation groups among qualifying patients with a mean sham SOL > 30 min (N = 19, representative subgroup from Teledyne study for this clinical trial). This led to a calculation suggesting that >12 patients per group will enable a comparison across ordered treatment groups for our primary outcome measure.

### 2.7. Recruitment

Participants will be recruited from eligible servicemembers, students, cadets, midshipmen, wounded warriors, and family members from a clinical population at the Walter Reed National Military Medical Center (WRNMMC). Recruitment efforts may include flyers, digital advertisements, email, word of mouth, and direct referrals from a physician. Interested participants will contact the study coordinator via phone or email to schedule an appointment for a screening, and an informed consent visit either at WRNMMC or USU will take place. We will enroll up to 60 patients with clinically diagnosed sleep-onset insomnia with a goal of 48 completing the study (assuming 20% attrition).

## 3. Expected Results

### 3.1. Anticipated Findings

We hypothesize that by applying SDR-tES across the forehead/mastoid for thirty minutes prior to attempting sleep, we can impose slow oscillations within the cortex during wakefulness, and the brain will be more likely to enter a sleep state. Our primary aim is to reduce the time to the onset of sleep by at least 50% from baseline in patients with a >30 min average SOL. Additionally, we will demonstrate that PeakSleep SDR-tES both reduces the time spent awake after sleep onset by 20% and improves the subjective benefits of sleep as measured by the ISI.

### 3.2. Statistical Analyses

Our primary outcome, the change in SOL from baseline as measured via FitBit actigraphy, will be assessed over 14 days of treatment data by constructing a linear mixed effects model accounting for age, baseline SOL, ISI severity, and prior sleep medication use. The changes related to the arm receiving the treatment first will be compared to those achieved by the group receiving the sham first, avoiding any persistent effects of the PeakSleep device. As a secondary outcome, within-subject comparisons between the treatment and sham will also be made using a linear mixed effects model, which will include the order as an additional covariate. Other secondary outcomes will be compared by similarly modeling the objective measures (TST, WASO) and subjective measures obtained at various timepoints across the trial (ISI, PHQ-9). To investigate the differences in sleep measures between treatment groups, we will analyze actigraphy data by evaluating measures of central tendency (the median within a patient and across nights) in each condition (the mean across patients comparing stimulation and sham treatments) imported into MATLAB (R2020). All measures will be investigated as differences from each patient’s individual baselines.

The immediate effects of the stimulation will also be investigated among physiological data, including heart rate and electroencephalography. Changes in heart rate variability and EEG spectral power will be assessed pre- versus post-stimulation, comparing intraindividual changes from baseline between the treatment and sham. For EEG spectral analysis, we will use MATLAB (R2020) to compute spectral power in each frequency band in response to each stimulation event.

The statistical significance of differences between treatment groups for each measure will be tested using either a Wilcoxon Rank Sum test or a paired Student’s *t*-test, depending on whether the data occupy a normal distribution. We will also perform a two-way ANOVA to investigate differences due to sex and the treatment order. A participant’s data will be assessed for inclusion in the study at each visit contingent on obtaining viable data in at least 8 out of the 14 daily sessions during each 2-week period, including viable actigraphy data and the accompanying sleep diary data, successful application of the PeakSleep™ intervention, and adverse events.

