## 2. Experimental Design

### 2.1. Study Design

The tES study (Wearable Neurotechnology for the Treatment of Insomnia) is a prospective, placebo-controlled, double-blind, crossover phase II clinical trial of a non-significant risk device used to treat individuals with sleep-onset insomnia. This study will be run as a single investigational site study with Teledyne Scientific & Imaging, LLC (Durham, NC, USA), as the Sponsor, and the Uniformed Services University of the Health Sciences (USU) as the trial investigation site. The study will involve five in-person visits to the study site, each separated by two weeks, for eight weeks total. Participants will be randomly assigned to either the short-duration repetitive–transcranial electrical stimulation (SDR-tES) intervention treatment or sham treatment condition on Visit 2 before crossing them over to the remaining condition on Visit 4. Each participant will receive a total of 14 days of exposure. Assignments will be counterbalanced among participants. Participants will not be followed up after the conclusion of the eight-week study.

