### 5.2. Visit 2 (Treatment 1)

Participants are block-randomized to treatment conditions based on the order (sham or stimulation first) and will be balanced with respect to gender. Participants who successfully complete 2 weeks of baseline collection will be enrolled in the first treatment group of their assigned order. To assess their insomnia baseline, they will complete the Insomnia Severity Index (ISI) during this visit. They will be trained on the use of the PeakSleep™ device and sent home for 2 weeks. The PeakSleep™ device will deliver therapy and collect EEG data for the investigation of neural activity for both stimulation and sham conditions. The participant’s response to the first treatment condition will also be measured with actigraphy and a daily sleep diary completed on a phone app, which also controls the PeakSleep™ device.

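### Order is randomised with balance on gender, but the primary mixed model does not name gender; if gender predicts change in SOL, the test is mildly conservative

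*Protocol article*

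**What the plan says.** Section 5.2 (Visit 2) describes the allocation: "Participants are block-randomized to treatment conditions based on the order (sham or stimulation first) and will be balanced with respect to gender". Section 2.1 adds "Assignments will be counterbalanced among participants", which implies 1:1 allocation to the two orders.

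Section 3.2 gives the primary analysis of change in SOL as "constructing a linear mixed effects model accounting for age, baseline SOL, ISI severity, and prior sleep medication use". Four covariates are named and gender is not among them. The same paragraph makes the primary contrast a comparison between order groups: "The changes related to the arm receiving the treatment first will be compared to those achieved by the group receiving the sham first". The within-patient comparison of stimulation and sham is secondary.

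Sex comes up later in Section 3.2, outside the primary model: "We will also perform a two-way ANOVA to investigate differences due to sex and the treatment order". The outcome, the period and the presence of an interaction term are not stated for that ANOVA.

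Section 2.7 sets the size: "We will enroll up to 60 patients with clinically diagnosed sleep-onset insomnia", "with a goal of 48 completing the study (assuming 20% attrition".

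**The concern.** When allocation is balanced on a factor that predicts the outcome, that factor contributes almost nothing to chance differences between the arms. A model that omits the factor still counts its variance as residual noise. The reported standard error is then larger than the true sampling variability of the estimate, the confidence interval is wider than it need be, and the test rejects less often than its nominal level.

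A crossover would normally be protected, because a patient's gender is the same in both periods. That protection does not reach the primary contrast here, which compares different patients. Change from baseline with adjustment for baseline SOL removes gender's link to the starting level, but not a link to the amount of change. At about 24 completers per arm, any precision given away is worth recovering if doing so costs almost nothing.

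**Working it through.** **Inputs from the protocol article.** 48 completers and up to 60 enrolled (Section 2.7); 1:1 allocation implied by counterbalancing (Section 2.1), so 48 / 2 = 24 per arm; gender-balanced allocation (Section 5.2); four covariates and a between-arm contrast (Section 3.2). The pilot effect size is d = 1.3 (Introduction), from a 23-participant crossover.

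**The plan's own figures.** 48 / (1 − 0.20) = 60, which agrees with Section 2.7. Section 2.6 states more than 12 per group. With d = 1.3, two-sided alpha 0.05 and 90% power, 2 × (1.960 + 1.282)² / 1.3² = 12.4, so 13 per group. That matches, but only conditionally: the article states neither alpha nor power, nor that d = 1.3 was the input (the calculation used a subgroup of 19).

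**Assumption.** Let R² be the share of patient-level residual variance in change in SOL that gender explains after the four listed covariates. The document gives no value, so a range is shown.

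**Analytic check.** With exact balance on gender:

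- ratio of model SE to true SE = 1 / √(1 − R²)
- actual two-sided type I error = 2 × [1 − Φ(1.96 / √(1 − R²))]

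At R² = 10%: 1 / √0.90 = 1.054; 1.96 × 1.054 = 2.066; type I error = 0.039.

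**Simulation check.** A linear model on patient-level change, 24 per arm, allocation balanced on gender, four other covariates fitted, with and without gender; 10,000 runs under the null and 8,000 under a true difference of 0.8 residual SD (illustrative, not from the document).

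| R² | SE ratio (analytic) | Type I error (analytic) | Type I error, no gender (simulated) | Power without / with gender at 0.8 SD |
|---|---|---|---|---|
| 0% | 1.00 | 0.050 | 0.050 | 73.2% / 73.1% |
| 5% | 1.03 | 0.044 | 0.048 | 74.2% / 75.4% |
| 10% | 1.05 | 0.039 | 0.039 | 73.3% / 76.7% |
| 20% | 1.12 | 0.028 | 0.032 | 75.4% / 82.2% |

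The power loss is therefore about 1, 3 and 7 points at R² of 5%, 10% and 20%. With gender in the model, simulated type I error lay between 0.047 and 0.054. With 25% women, the unadjusted type I error was 0.045 at R² = 5% and 0.026 at 20%.

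**Control.** With allocation not balanced on gender and R² = 20%, the model without gender had type I error 0.050. The conservatism therefore comes from balancing on gender and then omitting it.

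**Larger effect.** At 1.3 SD and 24 per arm, power without and with gender is 99.2% and 99.3% (R² 5%), 99.0% and 99.3% (10%), 98.6% and 99.3% (20%): a loss of under one point throughout.

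**Imperfect balance.** If patients are lost at random from 60 to 48, type I error without gender is 4.1% rather than 3.8% at R² = 10%, and 3.4% rather than 2.7% at R² = 20% (a separate simulation from the table). The effect shrinks.

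**The case against.** The strongest reply is that the effect may be nil. It needs gender to predict change in SOL after age, baseline SOL, insomnia severity and past sleep medication are in the model, and nothing in the document shows that it does. At R² of 5% or less the effect is negligible, and values of 10% to 20% have no support in the article. This stands: a reader might infer that the standard error is certainly too large, and the document does not support that.

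Second, the only effect size stated is d = 1.3, at which almost no power is lost. This also stands, with the reservation that a d from a crossover pilot may not carry over to a between-arm contrast.

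Third, a reader might infer that the separate two-way ANOVA can neither adjust the treatment effect for sex nor test whether it differs by sex. The text does not support that. On first-period change, order is the treatment arm, so an ANOVA on sex and order would give a sex-adjusted arm effect, and its interaction term would test effect modification. Section 3.2 specifies neither the outcome, the period nor an interaction, so one cannot say that the ANOVA does this or that it does not. Either way, it leaves the primary model's standard error unchanged.

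Fourth, randomisation factors are often settled in the SAP, which is not shown, and the article does not call its list exhaustive. That lowers the weight of the point. It does not remove it, because the article names four covariates for the primary model and the one characteristic it balances on is not among them.

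**Conclusion.** The mismatch between allocation and primary model is on the page and the direction is clear: conservative, never anti-conservative. The trial's validity is not at risk, since the estimate is unbiased and false positives are not inflated. A reading of the omission as a threat to the primary conclusion would go too far.

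The size rests on three assumptions: how strongly gender predicts change in SOL beyond the listed covariates, how well balance survives attrition and the rule on viable sessions, and the true effect. It ranges from zero (gender not prognostic) to a standard error about 12% too large (R² = 20%, exact balance). The secondary within-patient comparison is largely unaffected, because gender cancels there. This is a minor point, worth taking up because the remedy is nearly free.

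**What to change.** Add gender, in the form used for the randomisation, as a fixed effect in the primary mixed model. Use one term throughout, since Section 5.2 says *gender* and Section 3.2 says *sex*. Settle this before unblinding, so that there is no later choice between adjusted and unadjusted results.

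Optionally, specify any treatment-by-gender interaction within the same model and label it exploratory, or else state the outcome, period and terms of the two-way ANOVA.

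The cost is one degree of freedom and a line of wording. The planned gender balance and the ANOVA already require the variable.

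Label: free improvement, minor.

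### The secondary within-subject model adjusts for treatment order (sequence) but not for period, so a shift between the two treatment blocks inflates its standard error and, with unequal orders, biases its estimate

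*Protocol article*

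**What the plan says.** Section 3.2 describes several analyses.

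- **Primary.** Change in SOL from baseline is analysed by "constructing a linear mixed effects model accounting for age, baseline SOL, ISI severity, and prior sleep medication use". On the contrast itself, section 3.2 states: "The changes related to the arm receiving the treatment first will be compared to those achieved by the group receiving the sham first". The stated aim is to avoid persistent device effects, so I read this as a parallel comparison in the first treatment block.
- **Secondary.** Stimulation and sham are also compared within participants by a mixed model "which will include the order as an additional covariate". TST, WASO, ISI and PHQ-9 are to be modelled in a similar way.
- **Simple tests.** Differences between treatment groups will be "tested using either a Wilcoxon Rank Sum test or a paired Student" t-test, depending on normality. There is also a "two-way ANOVA to investigate differences due to sex and the treatment order".

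Section 5.2 fixes the meaning of order: participants are "block-randomized to treatment conditions based on the order (sham or stimulation first", which is the sequence group. Section 2.1 gives the timing as "five in-person visits to the study site, each separated by two weeks, for eight weeks total". With the visits in sections 5.1 to 5.5, this puts baseline in weeks 1–2, the first treatment block in weeks 3–4, washout in weeks 5–6 and the second block in weeks 7–8.

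**The concern.** In a two-period crossover, each participant's stimulation-minus-sham difference is also a difference between two calendar blocks. If SOL drifts between the blocks for any reason unrelated to the device, the drift enters that difference with opposite signs in the two sequences. A period term takes it out. A sequence term does not, because it moves both of a participant's values by the same amount.

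The article names the term added for the crossover, and that term cannot do this job. The other listed covariates are participant-level too. The ANOVA on sex and order is a separate test and does not adjust the treatment estimate. Subtracting the baseline does not help either: for SOL it is the first two weeks (section 5.1.1), it is common to both blocks, and it cancels from the contrast. A second baseline is named only for the ISI (section 5.4).

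At stake is part of the precision that section 6.1 claims for the repeated-measurement design and, if the analysed orders are unequal, some bias.

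**Working it through.** **Inputs.** From the article: 48 completers out of up to 60 enrolled with 20% attrition (section 2.7), which reproduces as 48 / (1 − 0.20) = 60. Assignments are counterbalanced (section 2.1). The article gives no figure for this model and no SD or period shift for SOL. I therefore assume an SD of the within-participant difference (sd) of 10, 15 or 20 min and a fall in SOL from block 1 to block 2 of 2, 5 or 10 min. The working uses one summary value per participant and block.

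**Algebra.** Let τ be the treatment effect, π the block 2 minus block 1 shift, nT and nS the numbers with stimulation first and sham first, and N = nT + nS. The expected stimulation-minus-sham difference is τ − π for stimulation first and τ + π for sham first. A sequence main effect cancels from both.

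Without a period term:
- bias = π(nS − nT)/N
- variance of the differences = sd² + π² · 4·nT·nS/N²

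With a period term, the estimate is the unweighted mean of the two sequence means, [(τ − π) + (τ + π)]/2 = τ, and the variance is sd².

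**Standard error inflation at 24/24.** Here 4·24·24/48² = 1, so the ratio is √(1 + π²/sd²):

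| Shift | sd 10 | sd 15 | sd 20 |
|---|---|---|---|
| 2 min | 1.02 | 1.009 | 1.005 |
| 5 min | 1.12 | 1.05 | 1.03 |
| 10 min | 1.41 | 1.20 | 1.12 |

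**Bias (stimulation minus sham) when SOL falls over time:**

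| Stimulation first / sham first | 5-min fall | 10-min fall |
|---|---|---|
| 24/24 | 0 | 0 |
| 26/22 | 5·4/48 = 0.42 min | 0.83 min |
| 28/20 | 5·8/48 = 0.83 min | 1.67 min |
| 30/18 | 5·12/48 = 1.25 min | 2.50 min |

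If more participants have stimulation first, the bias is against the device; if more have sham first, it favours the device.

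**Check by simulation.** Mixed models with a random participant intercept, sd = 10, no true effect, 300 data sets per setting:
- 24/24, 10-min fall: mean model SE 2.04 with order only, 2.04 with neither term and 1.43 with order and period. The formulas give √(200/48) = 2.04 and 10/√48 = 1.44. The estimate itself varied equally in all three (SD 1.51), so the order-only SE is simply too large. Rejection was 1.3% with order only and 6.7% with period; the latter is nominal within simulation error.
- 28/20, 10-min fall: mean estimate +1.78 with order only (formula +1.67) and +0.13 with period.
- 28/20, 5-min fall: +0.94 with order only (formula +0.83) and +0.10 with period.

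**How unequal might the orders be?** Assume 30/30 randomised and 12 losses at random. The orders then end unequal with probability 1 − C(30,6)²/C(60,12) = 75%. By the same hypergeometric count, they end at 22/26 or wider 33% of the time and at 20/28 or wider about 2% of the time. A split that wide would mainly reflect order-related dropout, or exclusions under the rule of 8 viable sessions out of 14.

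**The case against.** The case on the other side has real force on size.

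- **The model is secondary.** A reader might infer that the trial's main result is at risk. The documents do not support that. In the primary comparison, read as above, both arms are observed in the same block and no period term is needed. This stands.
- **The power loss depends on chosen values.** Take a correlation of 0.7 and a 0.5 SD shift at 24/24. The SE is √(0.60/48) = 0.112 SD with period and √(0.85/48) = 0.133 without. A true effect of about 0.31 SD then has roughly 80% power with period and Φ((0.31 − 1.96·0.133)/0.112) ≈ 67% without. At 0.5 SD the figures are about 99% and Φ((0.5 − 0.261)/0.112) ≈ 98%. None of these inputs is in the article, whose only effect size is the pilot's d = 1.3. A headline loss of power is therefore not supported.
- **Bias needs unequal orders.** Blocked, counterbalanced allocation keeps it small, and at equal orders the test is conservative. A reader might infer false efficacy claims; nothing here shows them. This stands.
- **Drift may be modest.** Two weeks of baseline precede block 1, so much regression to the mean would already have occurred. Only change between the two blocks counts. This also stands, and is why a range is given.
- **This may be condensation, or order may mean period.** This does not stand. The article chose to name the adjusting term, and section 5.2 uses the word for sequence. If period was meant, the wording conflicts with section 5.2 and still needs correcting.
- **Sequence is not wholly inert.** With 20% of participants lacking the second block, adding order moved the estimate by about 0.01 SD on average over 60 simulated fits. Essentially unchanged is therefore the right description.

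**Conclusion.** The point holds for the secondary within-subject SOL model, for any TST, WASO, ISI and PHQ-9 models of the same form, and for the plain stimulation-versus-sham tests. The stated term does not adjust for period, and nothing else in the article does.

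With equal orders the harm is an overstated standard error, negligible for a 2-min shift and up to 41% in the most extreme case assumed, with no bias. With unequal orders there is also a bias, under 1 min for a 5-min shift up to 28/20. These sizes rest wholly on the assumed SDs and shifts. The primary analysis is not touched, on the reading that it uses the first block only. This should be fixed, with the weight that belongs to a secondary analysis. It is not a threat to the trial's main conclusion.

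**What to change.** In section 3.2, specify every within-subject analysis as treatment + period + sequence + the listed baseline covariates, with a random participant effect and nights nested within participant-period. State that order means sequence.

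Replace the plain paired t-test or rank-sum test of stimulation against sham with a period-adjusted version: compute each participant's block 1 minus block 2 difference and compare the two sequences by a two-sample t-test or a rank-sum test. Half the difference between the sequence means estimates the treatment effect free of period.

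The cost is one degree of freedom and a change of wording. No extra data, visits or participants are needed.

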## Abstract

Sleep disruption and deprivation are epidemic problems in the United States, even among those without a clinically diagnosed sleep disorder. Military service members demonstrate an increased risk of insomnia, which doubles after deployment. This study will investigate the ability of a translational device, Teledyne PeakSleep™ (Teledyne Scientific & Imaging, Durham, NC, USA), to reduce sleep onset latency and the time spent awake after sleep onset, with improvement in the subjective benefits of sleep for patients with insomnia by enhancing the brain rhythms within the frontal lobe implicated in slow wave generation. During this crossover trial, patients will use the wearable neurotechnology prototype headband, which delivers < 14 min of frontal short duration repetitive–transcranial electrical stimulation over a 30 min period immediately before trying to fall asleep. Using active stimulation versus a sham paradigm, we will compare actigraphy data, physiological data, and subjective sleep measures against a pre-treatment baseline in the same patient over the course of the 8-week study. If successful, PeakSleep™ could address the final common pathway in insomnia, namely the onset and maintenance of slow-wave sleep (SWS), and accordingly has the potential to enhance sleep onset in a wide range of individuals, most importantly warfighters in whom efficient sleep onset may be critical for operational success.

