### 2.2. Primary Outcome

We intend to measure the reduction in SOL between sham and stimulation groups using FitBit actigraphy data collected during baseline, treatment, and washout periods.

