#### 5.1.1. Actigraphy Device Training

The participant will be trained on the device and asked to wear the actigraphy device (FitBit) continuously for the next 2 weeks. The first two weeks of the study involve collecting baseline sleep assessment data with a particular focus on identifying a pre-intervention SOL, which is the primary outcome.

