### 5.3. Visit 3 (Washout)

During Visit 3, we will collect PeakSleep™ devices and administer a second ISI to assess participants’ response to treatment condition 1. Participants will also be requested to fill out a short questionnaire asking about the occurrence and details of any adverse events during the past two weeks with the device, which the investigator will review during the visit. Participants will complete another PHQ-9 to reassess any impact on depression or suicidal ideations. Participants will return home without the PeakSleep™ device but will continue to wear the actigraphy devices and complete the daily sleep diary in order to monitor sleep habits during a 2-week washout period. The purpose of the washout interval is to investigate any lingering effects from the first intervention and to ensure that those receiving the stimulation first return to a proper baseline prior to the sham treatment. Visit 3 will take approximately 1 h.

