### 5.4. Visit 4 (Treatment 2)

Participants who were assigned to the stimulation treatment group during Visit 2 will be assigned to the sham group and vice versa. Participants will take the ISI once again for a second baseline measurement and will be sent home for the final 2 weeks to collect data on their responses to the second treatment condition. Their response to the second treatment condition will be measured with actigraphy and a daily sleep diary. EEG data will also be collected again from PeakSleep™ for the investigation of neural activity. Visit 4 will take approximately 30 min.

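### For the secondary within-patient ISI comparison, the change-from-baseline rule leads to subtracting the Visit 4 ISI, which can cost precision (variance ratio up to 2) and lets carryover into the contrast

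*Protocol article*

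**What the plan says.** Section 3.2 sets one rule for all outcomes: "All measures will be investigated as differences from each patient’s individual baselines". It does not say which baseline applies in the second treatment period.

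For the ISI, the procedures supply two candidates. At Visit 2: "To assess their insomnia baseline, they will complete the Insomnia Severity Index (ISI) during this visit". At Visit 4, after the washout: "Participants will take the ISI once again for a second baseline measurement". The end-of-period ISI values are taken at Visits 3 and 5 (sections 5.3 and 5.5, Table 2).

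For actigraphy the article points to one baseline only. Section 5.1.1 says: "The first two weeks of the study involve collecting baseline sleep assessment data with a particular focus on identifying a pre-intervention SOL". The abstract speaks of comparing "subjective sleep measures against a pre-treatment baseline in the same patient over the course of the 8-week study". The washout is there to detect lingering effects and to "ensure that those receiving the stimulation first return to a proper baseline prior to the sham treatment".

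Section 3.2 makes the primary SOL analysis a comparison of the two sequence arms, with baseline SOL as a covariate. The within-patient comparison is secondary, by mixed model with order as a covariate, and the ISI is to be modelled similarly. The section also provides for a paired t-test or a Wilcoxon test for each measure. Section 3.1 names the ISI as the measure of subjective benefit.

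**The concern.** In a crossover each patient already serves as his or her own control. Taking the end-of-stimulation value minus the end-of-sham value removes stable differences between patients. Subtracting a different baseline in each period removes no more of that stable variation, but brings in the measurement error of two further ISI values. It helps only when a period's baseline shares a good deal of that period's transient variation.

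The Visit 4 baseline also follows the first treatment. In patients who had stimulation first, anything left of its effect at Visit 4 becomes part of the sham change.

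At stake are the precision and direction of the within-patient ISI result. The choice of baseline would also remain open until the data are seen.

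**Working it through.** **Inputs.** ISI at Visits 2, 3, 4 and 5, written V2 to V5 (sections 5.2 to 5.5, Table 2). Visits are two weeks apart (section 2.1). Section 2.7 aims for 48 completers from 60 enrolled, which reproduces: 60 × 0.8 = 48. The article gives no ISI standard deviation, correlation or effect size, so it has no variance figure to reproduce. Correlations and effect sizes below are assumptions, shown as ranges, with equal variance at each visit.

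**Step 1: the contrasts.** Direct: V3 − V5. Change score: (V3 − V2) − (V5 − V4) = (V3 − V5) − (V2 − V4). If one common baseline is used in both periods it cancels: (V3 − V2) − (V5 − V2) = V3 − V5, a ratio of 1.00.

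**Step 2: general formula.** Let β be the slope of V3 − V5 on V2 − V4. If these two differences have equal variance, then relative to the direct contrast:
- raw subtraction has variance ratio 1 − 2β + 1 = 2 − 2β;
- using V2 − V4 as a covariate has ratio 1 − β².

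Subtraction therefore gains only if β exceeds 0.5. The covariate version never exceeds 1 in large samples.

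**Step 3: three correlation structures.**
- Equal correlation: β = 0.
- AR(1), correlation ρ per two weeks: β = (ρ − ρ³) / [2(1 − ρ²)] = ρ/2, so subtraction gives 2 − ρ and the covariate gives 1 − ρ²/4.
- Correlation w within a period and r between periods: β = (w − r)/(1 − r).

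| Structure | Subtraction | Covariate |
|---|---|---|
| Equal correlation, any value | 2.0 | 1.00 |
| AR(1), ρ = 0.3 | 1.7 | 0.98 |
| AR(1), ρ = 0.5 | 1.5 | 0.94 |
| AR(1), ρ = 0.7 | 1.3 | 0.88 |
| AR(1), ρ = 0.9 | 1.1 | 0.80 |
| w = 0.6, r = 0.5 | 1.6 | 0.96 |
| w = 0.75, r = 0.5 | 1.0 | 0.75 |
| w = 0.8, r = 0.5 | 0.8 | 0.64 |

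A simulation with equal between- and within-patient variance agrees: variance 1.99 for the direct contrast, 1.99 with a common baseline, 3.99 with separate baselines.

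**Step 4: what this means for 48 completers.** At ratio 2.0 they carry the information of 48/2 = 24 patients, and at ratio 1.1 that of 48/1.1 ≈ 44. Power of a two-sided 5% paired t-test, for assumed standardised paired effects:

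| Effect | Ratio 1.0 | 1.3 | 1.5 | 2.0 |
|---|---|---|---|---|
| 0.413 (set to give 80%) | 80% | 69% | 63% | 51% |
| 0.5 | 92% | 85% | 79% | 67% |
| 0.8 | 100% | 100% | 99% | 97% |

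**Step 5: carryover.** Let stimulation lower the ISI by τ. In stimulation-first patients let fractions L4 and L5 of that effect remain at Visits 4 and 5. Sham-first patients contribute −τ either way. Averaged over balanced sequences:
- direct contrast: −τ(1 − L5/2);
- change-score contrast: −τ(1 + (L4 − L5)/2).

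With L4 = 0.3 and L5 = 0, the change score overstates the benefit by 15% and the direct contrast is unbiased. With L4 = L5 = 0.3, the change score is unbiased and the direct contrast understates the benefit by 15%. Subtraction gives the larger bias when L5 is below L4/2, that is, when more than half of what lingers at Visit 4 has gone by Visit 5.

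**Step 6: the primary analysis.** With baseline as a covariate, modelling change or the post-treatment value gives the same treatment estimate (−10.4465 both ways in a simulated data set). There is no loss there.

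**The case against.** The strongest reply is that the article never says Visit 4 is subtracted. The plural in "All measures will be investigated as differences from each patient’s individual baselines" may simply cover several patients and measures. The Visit 4 ISI could serve only the washout check that patients "return to a proper baseline prior to the sham treatment". The PHQ-9, also analysed in 3.2, has no Visit 4 value in Table 2, so the sentence cannot mean a post-washout baseline for everything. An analysis plan not shown may settle the matter.

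Much of this stands. A reader might infer that every measure, SOL included, suffers a doubled variance. The documents do not support that. SOL has one named pre-treatment baseline, which cancels. Section 2.2 says only that data are "collected during baseline, treatment, and washout periods", which does not make washout nights a subtracted baseline. The primary analysis compares arms and adjusts for baseline. The sample size in 2.6 rests on mean SOL, not on change scores, so it is not called into question either.

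For the ISI the reply is weaker. The article states a change-from-baseline rule and itself labels both Visit 2 and Visit 4 as baselines. Subtracting each period's own baseline is the natural result of what is written, not a detail passed over in silence.

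It is also fair that the loss is not certain: strong within-period correlation brings the ratio to 1 or below. The schedule makes this less likely, because Visits 3 and 4 are as close in time as Visits 2 and 3. If correlation depends only on the gap, with r1, r2 and r3 at two, four and six weeks, the ratio is 2 − (r1 − r3)/(1 − r2). This lies between 1 and 2 whenever correlation falls with the gap at a non-increasing rate. Finally, subtraction removes carryover that persists unchanged to Visit 5, so the bias argument runs both ways.

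**Conclusion.** The point holds for the secondary within-patient ISI comparison only. As written, 3.2 with 5.2 and 5.4 leads to (V3 − V2) − (V5 − V4). Its variance relative to V3 − V5 is 2.0 under equal correlation and 2 − ρ under AR(1), that is 1.7 to 1.1 for ρ from 0.3 to 0.9. This assumes equal variance at each visit. The documents give no correlation, so this is a range, and a ratio of 1 or less remains possible.

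The direction of any carryover bias depends on timing. It favours the device if the effect is present at Visit 4 and mostly gone by Visit 5. Subtraction reduces bias if the effect persists to Visit 5.

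The practical loss is material for a moderate paired effect (80% power falling to 51% at worst) and small for a large one (97% remains at 0.8). The primary SOL result is untouched. SOL, TST and WASO are untouched as long as the first-fortnight baseline serves both periods. The change should be made, because the covariate alternative is, in large samples, never less precise than either subtraction or no adjustment.

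**What to change.** In section 3.2, or in the analysis plan before unblinding, state the following.

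- The within-patient ISI comparison uses the end-of-period values at Visits 3 and 5, with treatment and period as fixed effects and patient as a random effect. The Visit 4 ISI is not subtracted.
- If period baselines are used, the within-patient difference Visit 2 minus Visit 4 enters as a covariate. The analysis without it is then reported as a sensitivity check for carryover. The Visit 2 ISI alone would not serve this purpose: it is constant within a patient and, with complete data, does nothing for the within-patient contrast.
- SOL, TST and WASO use the single pre-treatment fortnight as baseline in both periods. Washout values only describe return to baseline.

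The cost is wording alone, with no new data or visits. The per-period ISI change score can still be tabulated, but becomes descriptive.
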